- 1. Preliminary data

Within the Stockholm Diabetes Prevention Programme (SDPP), a baseline study was performed during 1992-1998 . The prevalence of diagnosed T2D and family history of diabetes was mapped by a questionnaire to all subjects, 35-55 years old, in five Stockholm County municipalities. From this sample, a total of 3128 men (1992-1994) and 4821 women (1996-1998), none with previously diagnosed diabetes, but 50% with family history of diabetes (FHD), were investigated with oral glucose tolerance test (OGTT), body measurements (weight, height, waist, blood pressure etc), and an extensive questionnaire about lifestyle (i.e. food, exercise, tobacco, alcohol habit) and psychosocial and socio-economical issues related to working and family life, education, social network, and stress. In this baseline study, we found 65 men with diabetes (2.1%) and 228 men with prediabetes (IFG and/or IGT) (7.3%), and 63 women with diabetes (1.3%) and 208 with prediabetes (4.3%).

In the follow-up study 8-10 years later (2003-2006), we repeated a similar investigation, including OGTT and the same questionnaire as at baseline, in more than 70% of the baseline study participants. At follow-up, like at baseline, men had a two-fold higher prevalence of T2D and prediabetes (7.7% and 12.0%, respectively) compared with women (3.3% and 6.2%, respectively). Thus, of men with normal glucose tolerance at baseline we found a total of 111 with diabetes and 255 with prediabetes, and of women with normal glucose tolerance at baseline we found 60 with diabetes and 181 with prediabetes. In addition, there were 72 men and 46 women with prediabetes at baseline, who had developed manifest T2D at follow-up.

1. Endpoints
   1. Primary Endpoint

To test whether there is a difference in the mean change in first-phase plasma insulin response at the hyperglycemic clamp investigation [44] at visit 4 (8 weeks) compared to baseline, between patients receiving vitamin D3 30000 IU weekly for 8 weeks vs. placebo. Insulin will be measured at minutes 0, 2, 4, 6, 8 and 10. Increment from minute 0 in area-under-curve (AUC) will be computed and used for the statistical analyses.

- 1. Secondary Endpoints
     1. Secondary Efficacy Endpoints

To test whether there is a difference in the mean change in late phase insulin response (10-120 minutes) during hyperglycemic clamp at visit 4 (8 weeks) compared to baseline, between patients receiving vitamin D3 30000 IU weekly for 8 weeks vs. placebo.

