Unless otherwise specified, all tests will be two-sided at 5 % significance level. Correction for multiple secondary endpoints will not be performed. Results of all endpoints will be presented irrespective of statistical significance. Further, all primary and secondary endpoints will also be summarized by descriptive statistics.

- - 1. Endpoints

See section 6.

- - 1. Analysis of efficacy endpoints

The primary efficacy analysis will test for differences between arm A and B in the change from baseline in insulin response at the hyperglycemic clamp investigationafter 8 weeks of treatment. The non-parametric Mann-Whitney U test will be used primarily. The Wilcoxon matched pairs test will be used for within group analyses. If data permits (i.e. normal distribution), parametric tests will also be used. Multiple regression analysis will be performed to adjust for age, sex and other baseline characteristics, if necessary.

- - 1. Analysis of safety endpoints

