#### Other safety endpoints

Other safety endpoints will summarized by descriptive statistics:

- Clinically relevant change in physical examination
- Occurrence of hypercalcemia, defined as free s-calcium > 1.35 mmol/l
- Occurrence of plasma levels of 25-OH-Vitamin D > 250 nmol/l
- Clinically relevant change in plasma hematology
- Clinically relevant change in plasma biochemistry
  1. Determination of Sample Size

The present study is considered as a pilot study. No similar publicized study has been found that could provide data for a formal power calculation. A recent randomized trial with a cytokine suppressor could demonstrate a significant increase first phase insulin secretion, the effect being slightly less than 30 % [45]. In this study, treatment and control groups comprised of 20 individuals each. Several previous studies performed at our own unit on insulin sectretion and insulin sensitivity have been successfully carried out in groups of 10-15 individuals. We will therefore expect that18 subjects should be available for analysis in each arm. To allow for using a non-parametric test about 5 % more patients are needed (Lehmann 1975) and thus 19 subjects in each arm should be included in the final analysis. To compensate for study drop-out, 22 subjects should be randomized to each treatment arm. Thus 44 subjects should be included in the study. With a screening failure rate of 30 %, about 58 subjects need to be screened.

1. Direct Access to Source Documents

The Investigator has the responsibility that a secrecy agreement is established between the clinic and the monitor, giving the permission to verify data in the patients´ hospital records. Signed informed consent will be obtained from the subjects prior to any trial-related activity regarding this matter.

1. Quality Control
   1. Source Data

Information in each patients hospital records will include information on study participation study title, randomization number, informed consent, diagnose, the two different study treatments, who to contact regarding questions about the trial and where the randomization codes are kept.

- - 1. The following template will be used at visit 1:

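### The primary Mann-Whitney test on change scores is valid, but the protocol plans no adjustment for the baseline insulin AUC, which costs efficiency at 19 per arm

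*Protocol*

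**What the plan says.** Section 6.1 poses the primary question as a comparison of arms: "To test whether there is a difference in the mean change in first-phase plasma insulin response". The variable is defined there too: "Increment from minute 0 in area-under-curve (AUC) will be computed and used for the statistical analyses".

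Section 12.2.2 sets the comparison: "The primary efficacy analysis will test for differences between arm A and B in the change from baseline in insulin response". It then names the test: "The non-parametric Mann-Whitney U test will be used primarily". Two supplementary analyses follow, each with a condition attached:

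- The first depends on the shape of the data: "If data permits (i.e. normal distribution), parametric tests will also be used".
- The second, covariate adjustment, depends on a need that is not defined: "Multiple regression analysis will be performed to adjust for age, sex and other baseline characteristics, if necessary".

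Section 12.2 sets the level: "Unless otherwise specified, all tests will be two-sided at 5 % significance level". Section 12.3 calls the trial a pilot and explains the lack of a power statement: "No similar publicized study has been found that could provide data for a formal power calculation". It starts from 18 per arm, adds about 5% for the rank test, and arrives at 19 per arm analysed and 22 randomised.

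**The concern.** The baseline clamp is done in every subject at the randomisation visit, so the baseline first-phase AUC is already in hand. The primary analysis uses it only by subtraction. Subtraction imposes a slope of 1 on baseline. When the true slope is lower, part of the baseline variation stays in the change score as noise.

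Adjustment appears only in the supplementary regression. No criterion says when that is needed, the covariate list is open, and baseline insulin response is not named. It could enter only as one of the unnamed other characteristics.

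At stake is avoidable loss of power in a trial of 38 analysed subjects with no formal power calculation. There is also an adjusted analysis whose existence and content may be settled after the data are seen.

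**Working it through.** **The plan's own figure.** 18 × 1.05 = 18.9, rounded up to 19 per arm. The efficiency of Mann-Whitney against the t-test under normality is 3/π, and 18/(3/π) = 18.85, again 19. The allowance reproduces. It covers the rank test's loss against a t-test on the same change scores, not the loss from leaving baseline unadjusted.

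**Inputs.** From the protocol: 19 per arm, 1:1 allocation, two-sided 5%. Assumed, because the protocol gives neither an SD nor a correlation: equal variance s² at both visits and r from 0.3 to 0.9.

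**Variance.** Change score: 2s²(1 − r). ANCOVA with baseline as covariate: s²(1 − r²). Ratio: (1 − r²)/[2(1 − r)] = (1 + r)/2.

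| r | Ratio | 19/ratio: per-arm size with the same precision under a change-score t-test |
|---|---|---|
| 0.3 | 0.65 | 29.2 |
| 0.5 | 0.75 | 25.3 |
| 0.7 | 0.85 | 22.4 |
| 0.8 | 0.90 | 21.1 |
| 0.9 | 0.95 | 20.0 |

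These ratios apply to parametric ANCOVA only.

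**Simulated power.** 19 per arm, 4000 replicates per setting. The true difference is (1.960 + 0.842) × √(2/19) = 0.909 SD of the change, nominally 80% power for a change-score t-test. Outcomes are normal, or log-normal with log SD 0.7. The rank version here is ordinary ANCOVA on ranks. Power in %:

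| r | Normal: Mann-Whitney | Normal: ANCOVA | Normal: rank ANCOVA | Log-normal: Mann-Whitney | Log-normal: raw-scale ANCOVA | Log-normal: rank ANCOVA | Log-normal: log-scale ANCOVA |
|---|---|---|---|---|---|---|---|
| 0.3 | 74.4 | 91.5 | 89.8 | 80.5 | 83.3 | 90.9 | 92.3 |
| 0.5 | 73.3 | 87.6 | 84.9 | 77.6 | 76.1 | 84.6 | 87.4 |
| 0.7 | 74.1 | 83.3 | 78.0 | 75.0 | 69.5 | 78.9 | 83.6 |
| 0.8 | 74.7 | 80.7 | 73.7 | 74.9 | 67.6 | 74.8 | 81.5 |
| 0.9 | 75.2 | 79.9 | 68.6 | 70.9 | 63.7 | 69.3 | 79.4 |

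With no true difference, Mann-Whitney rejected in 4.0% to 5.1% of replicates.

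**Second simulation.** This used the Quade test itself, with Mann-Whitney power of about 73% to 82%. ANCOVA on a near-normal scale gained about 15 points at r = 0.3, 9 to 12 at 0.5, 8 at 0.7 and 4 to 8 at 0.9. Quade gained about 10 to 14 at 0.3, 6 to 9 at 0.5 and 3 to 4 at 0.7, nothing at 0.8, and lost 3 to 5 at 0.9. The two runs agree within about three points. I carry the second forward because it uses the test proposed below.

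**Reading.** ANCOVA on a suitable scale beats Mann-Whitney at every r tried. The rank version does so only up to about r = 0.7. Raw-scale ANCOVA on skewed data is worse from r = 0.5 upward. The choice of scale therefore matters as much as the covariate.

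**The case against.** **The primary analysis is already fixed.** A reader might infer that three analyses compete and that the choice is open once the data are seen. The text does not support that. Mann-Whitney is named as primary, the parametric tests are additions to it, and section 12.2 commits to presenting all endpoints whatever their significance. Only the supplementary analyses depend on the data.

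**The test is valid.** A reader might infer that chance baseline imbalance biases the primary result. Averaged over randomisations it does not, and the error rate stays near 5%. Imbalance is one of the sources of the extra variance computed above, so counting it as a second fault would count it twice.

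**Mean change.** Section 6.1 speaks of a mean change, which Mann-Whitney does not estimate. Quade does not either, so this is no argument for replacing one rank test with the other. It supports only the request for a stated effect estimate.

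**The gain is not known.** It rests wholly on an assumed r. A population running from impaired fasting glucose to diabetes may vary widely at baseline, which tends to raise r, and there the gain is smallest. This stands, and it limits how strongly the point can be put.

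**A SAP may list the covariates.** It may, and the protocol's wording does not exclude baseline insulin response. But the protocol itself fixes an unadjusted primary test and makes adjustment conditional, so this part is not merely left to a later document.

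**Conclusion.** The point holds as one of efficiency. The pre-specified primary test is sound, but it makes no planned use of the baseline AUC as a covariate, and the only adjusted analysis has no stated trigger and no closed covariate list.

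The loss is material if r is about 0.7 or less and the adjusted analysis is run on a suitable scale. At r of 0.8 to 0.9 it is modest for a well-scaled ANCOVA and absent or reversed for the rank version. These sizes assume equal variances at the two visits and normal or log-normal outcomes. None of them shows the primary test to be invalid or its choice to be open.

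**What to change.** In section 12.2.2, pre-specify one baseline-adjusted analysis as primary: week-8 incremental first-phase AUC by arm, with baseline incremental AUC as covariate. Name the scale before unblinding, as one of:

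- ANCOVA on a stated normalising transformation. It must tolerate zero or negative increments, which a plain logarithm does not; an inverse hyperbolic sine with a stated constant is one possibility.
- Quade rank ANCOVA, if r is expected to be no more than about 0.7.

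Report the adjusted between-arm difference with its 95% confidence interval on that same scale. Close the covariate list, delete the conditional phrase that ends the regression sentence, and keep the unadjusted Mann-Whitney as a sensitivity analysis.

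The cost is wording and one degree of freedom (38 − 3 = 35 residual instead of 38 − 2 = 36). No new data, visits or subjects are needed. The downside is little gain if r turns out to be 0.8 to 0.9, or a small loss with the rank version near 0.9.

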#### Adverse events, serious adverse events and adverse reactions

Adverse reactions and serious adverse events will be coded using Medical Dictionary for Regulatory Activities (MedDRA) and summarized by treatment group, MedDRA system organ class, MedDRA preferred term, severity and relation to trial product. All adverse events will be listed.

For an AE to be an AR the suspected association between the product and the unwanted medical condition should be at least a reasonable ***possibility***. This include if they occur between first trial drug date and until 7 days after last trial drug date. Events occurring outside this interval are not classified as AR; hence they will not be included in the summaries.

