To test whether there is a difference in the mean change in insulin sensitivity assessed as the ratio of the glucose infusion rate and plasma insulin concentration (M/I) during hyperglycemic clamp at visit 4 (8 weeks) compared to baseline, between patients receiving vitamin D3 30000 IU weekly for 8 weeks vs. placebo.

To test whether there is a difference in the mean change in glucose tolerance assessed by an oral glucose tolerance test (OGTT) at visit 4 (8 weeks) compared to baseline, between patients receiving vitamin D3 30000 IU weekly for 8 weeks vs. placebo.

To test whether there is a difference in the mean change in fasting plasma glucose and HbA1c at visit 4 (8 weeks) compared to baseline, between patients receiving vitamin D3 30000 IU weekly for 8 weeks vs. placebo.

To test whether there is a difference in the mean change in CVD risk markers/lipids at visit 4 (8 weeks) compared to baseline, between patients receiving vitamin D3 30000 IU weekly for 8 weeks vs. placebo.

To test whether there is a difference in the mean change in hormones as leptin, adiponectin and GLP-1 at visit 4 (8 weeks) compared to baseline, between patients receiving vitamin D3 30000 IU weekly for 8 weeks vs. placebo.

To test whether there is a difference in the mean change in 25-OH-vitamin D and PTH at visit 4 (8 weeks) compared to baseline, between patients receiving vitamin D3 30000 IU weekly for 8 weeks vs. placebo.

- - 1. Safety Endpoints

To compare the intervention with vitamin D3 compared to placebo in:

- Incidence of hypercalcemia defined as free s-calcium > 1.35 mmol/l at week 4 and 8.
- Laboratory assessments (hematology, biochemistry).
- Physical examination.
- Adverse events regarding incidences, intensity, severities and causality.

1. Design
   1. Outline

The trial is a randomized, parallel groups, double-blind, placebo-controlled trial with an 8 weeks intervention period. The trial will include a screening visit to assess the eligibility of the subjects. At the randomization visit the baseline investigations will be performed and the subjects will be randomized to one of two intervention arms:

- In the first treatment arm (arm A), subjects will receive vitamin D3 intervention, 30000 IU given orally once weekly. After 8 weeks the investigations will be repeated.
- In the second treatment arm (arm B), subjects will receive matching placebo once weekly. After 8 weeks the investigations will be repeated.

Figure: Trial design

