- 1. Visits and telephone contacts
- Visit 1 (Screening, week -2): Patient information, informed consent and eligibility. OGTT.
- Telephone 1 (week -1): Eligibility.
- Visit 2 (Randomization, week 0): Hyperglycemic clamp. First dose of study treatment.
- Telephone 2 (week 1). Compliance. Second dose of study treatment.
- Telephone 3 (week 2). Compliance. Third dose of study treatment.
- Telephone 4 (week 3). Compliance. Fourth dose of study treatment.
- Visit 3 (week 4). Safety and fifth dose of study treatment.
- Telephone 5 (week 5). Compliance. Sixth dose of study treatment.
- Telephone 6 (week 6). Compliance. Seventh dose of study treatment.
- Telephone 7 (week 7). Compliance. Eighth dose of study treatment.
- Visit 4 (week 8+0d and week 8+1d). End-of-study investigations (OGTT + hyperglycemic clamp).
- Telephone 8 (week 9). Follow-up safety.
  1. Assessments and Procedures
     1. Recruitment of subjects

Subjects are recruited from the database of the SDPP. Subjects who at follow-up were categorized as having IFG, IGT or IFG + IGT (N=366) at the follow up performed in the years 2003 - 2006 will be contacted for the present study. The screening period will start in Q3 2011. An OGTT will be performed at screening and subjects still having one of the three pre-diabetic conditions, or diet treated diabetes type 2 will be eligible for the study.

1. Selection and Withdrawal of Subjects

The sample size estimation (see section 12.3) requires that 38 subjects should complete the study to investigate the primary endpoint. To compensate for study drop-out, a total of 44 male or female subjects will be included in the study. With a screening failure rate of 30 %, about 58 subjects need to be screened.

- 1. Inclusion Criteria

1. Informed consent obtained before any trial-related activities[[1]](#footnote-2).
2. Meeting criteria for IFG, IGT, IFG+IGT or diabetes mellitus at the screening OGTT.
   - IFG = fasting p-glucose 6.1-6.9 mmol/l
   - IGT = 2 hour p-glucose 7.8-11.0 mmol/l
   - Diabetes = fasting p-glucose ≥ 7.0 mmol/l and/or 2 hour p-glucose ≥ 11.1 mmol/l
3. Age  45 and  75 years, female or male.
4. BMI ≤ 32 kg/m2.
5. HbA1c  ≤ 7.0 % (MonoS) or ≤ 63 mmol/mol (IFCC).
6. Fasting plasma glucose < 9 mmol/l.
7. S-25-OH-vitamin D3 < 75 nmol/l.
8. Able and willing to perform tests and examinations specified in the protocol.
   1. Exclusion Criteria
9. Previous participation in this trial. Participation is defined as randomization.

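### The 7-day rule denies adverse-reaction status to late-onset events whatever the investigator judges, and by-arm tabulation is specified only for adverse reactions and SAEs

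*Protocol*

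**What the plan says.** **The window.** Section 12.2.3 of the protocol, under its adverse-event subheading, repeats the test that an adverse reaction needs a reasonable possibility of association with the product. It then adds a calendar condition: "This include if they occur between first trial drug date and until 7 days after last trial drug date". The consequence follows at once: "Events occurring outside this interval are not classified as AR; hence they will not be included in the summaries".

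**The schedule.** Section 7.2 places the last dose and the contacts after it as follows:
- The final home dose falls at this call: "Telephone 7 (week 7). Compliance. Eighth dose of study treatment".
- The closing investigations come a week later and take two days: "Visit 4 (week 8+0d and week 8+1d). End-of-study investigations (OGTT + hyperglycemic clamp".
- The last planned contact of all is one more call: "Telephone 8 (week 9). Follow-up safety".

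**The definition elsewhere.** Section 11.1.2 has the investigator classify each adverse event as related or not related, with no time limit. Section 11.3 has adverse events collected until the study ends and asked about at every visit and call.

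**The tabulation.** Section 12.2.3 plans MedDRA coding and a summary by treatment group for adverse reactions and serious adverse events. For the rest it says "All adverse events will be listed". Section 6.2.2 gives as a safety endpoint the comparison of vitamin D3 with placebo in "Adverse events regarding incidences, intensity, severities and causality". Section 12.2 says in general terms that all primary and secondary endpoints will be summarised descriptively.

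**The concern.** There are two separate problems.

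First, a calendar rule in the statistics section overrides a causality judgement that section 11.1.2 gives to the investigator. An event that starts after the window and is rated probably related would be an adverse reaction under 11.1.2 and not one under 12.2.3. The week-9 call exists for safety follow-up, yet nothing that begins in the week before it can enter the adverse-reaction summary.

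Second, the table specified by arm depends on attribution. In a double-blind randomised trial, the comparison of all events between arms does not rely on a case-by-case causality judgement. If only adverse reactions and SAEs are coded and tabulated, non-serious events rated unlikely to be related appear in the listing but in no table that this section specifies. The endpoint in 6.2.2 concerns adverse events, not only adverse reactions.

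**Working it through.** The plan gives no figure to reproduce. The check is calendar arithmetic on section 7.2, followed by a comparison of passages.

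**Inputs.** Week 0 is day 0. Doses are at weeks 0 to 7. The window runs "between first trial drug date and until 7 days after last trial drug date" (section 12.2.3).

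**Nominal schedule.**
- Last dose: 7 × 7 = day 49.
- Window closes: 49 + 7 = day 56.

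| Contact | Day | Relative to window end |
|---|---|---|
| Visit 4, first day (week 8+0d) | 56 | inside, last day |
| Visit 4, second day (week 8+1d) | 57 | 1 day outside |
| Telephone 8 (week 9) | 63 | 7 days outside |

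The days on which a new onset cannot be an adverse reaction are 57 to 63, which is 7 days. Of the 63 − 49 = 14 days after the last dose, that is 7/14, or half. Of all days 0 to 63 (64 days), it is 7/64 = 10.9%.

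**If the last dose is late.** With the contacts unchanged and the dose d days late, the window closes on day 56 + d. Day 57 falls inside once d is 1 or more. Day 63 stays outside for any d below 7.

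**If dosing stops early.** With the last dose at week w, the window closes on day 7w + 7, and the gap to day 63 is 63 − (7w + 7) = 56 − 7w days. For w = 7 this is 7 days; for w = 4 it is 28 days. This assumes that such a subject is still followed to the scheduled week-9 contact.

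**Onset or report.** The rule turns on when an event occurs. An event that starts on day 55 and is first mentioned on day 63 is inside. One that starts on day 60 is outside.

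**What is tabulated by arm.**

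| Event type | Section 12.2.3 | Endpoint in 6.2.2 |
|---|---|---|
| Adverse reaction, onset in window | coded, summarised by arm, listed | covered |
| SAE, onset in window | coded, summarised by arm, listed | covered |
| Event judged related, non-serious, onset after window | listed only | covered |
| SAE, onset after window | unclear | covered |
| Non-serious event judged unlikely related | listed; no by-arm table specified | covered |

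The fourth row is unclear because the summaries referred to cover adverse reactions and SAEs alike, while the reason given for exclusion applies only to adverse reactions.

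**The case against.** The other side has several fair points.

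- **No data are lost.** Every adverse event is asked about, recorded, followed up and listed. With 44 subjects, a full listing shows everything. This stands: what is lost is the adverse-reaction classification and a place in the summary.
- **The week-9 call is not excluded.** A reader might infer that whatever is reported there is ignored. The text does not support that, because the rule goes by onset date. For Visit 4 a single day is at issue, and it falls inside if the last home dose is taken a day late.
- **A general promise exists.** The safety endpoints sit under the secondary-endpoint heading in section 6.2, and section 12.2 promises descriptive summaries of all secondary endpoints. So it would be too strong to say that non-serious events judged unrelated can appear in no by-arm table. Further table layouts may also be left to an analysis plan. What remains is that the adverse-event text is narrower than both the endpoint and the general promise.
- **A fixed window is a recognisable convention.** Seven days is one dosing interval, day 56 ends the 8-week intervention period, and section 9.6 says there is no active follow-up after treatment. This would justify an on-treatment display. It does not justify stating that later events are not adverse reactions, which contradicts 11.1.2.
- **The main vitamin D signals are handled elsewhere.** Hypercalcemia, high 25-OH-vitamin D, physical examination, hematology and biochemistry are summarised separately in 12.2.3 without the 7-day limit. This stands.

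**Conclusion.** The point holds as a conflict between stated rules. On the nominal schedule, new onsets on days 57 to 63 are denied adverse-reaction status by date alone, against the untimed investigator judgement in section 11.1.2. This affects half of the 14 days after the last dose and about 11% of days 0 to 63. The gap lengthens by 7 days for each weekly dose missed at the end, provided the subject is followed to week 9. Separately, the tabulation specified by arm covers only adverse reactions and SAEs, which is narrower than the endpoint in 6.2.2 and the general promise in 12.2.

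Two stronger readings are not supported. One is that safety data are discarded: all events are still recorded and listed. The other is that SAEs after day 56 are definitely left out of the summaries: the wording is ambiguous, which is a reason to rewrite it but not proof that they are dropped.

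The day counts assume dosing and contacts on schedule. The number of affected events cannot be derived from the protocol. Efficacy and the separately summarised calcium and laboratory safety endpoints are not affected.

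**What to change.** In section 12.2.3:

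1. Delete the sentence that reclassifies later events, and let adverse-reaction status follow the investigator's judgement as in 11.1.2.
2. Summarise by arm all adverse events with onset from the first dose to the subject's last safety contact (Telephone 8 for completers): number of subjects with an event, intensity and causality, with adverse reactions and SAEs as subsets. Tie the end of the interval to that contact and not to a fixed 14 days, which would not fit subjects who stop dosing early.
3. State that SAEs are summarised over the same interval, which removes the ambiguity.
4. If an on-treatment view is wanted, keep the 7-day window as an additional display.

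The cost is MedDRA coding of all adverse events instead of only adverse reactions and SAEs, one more table, and a few unrelated late events in the summaries. No extra data collection is needed, because the events are already elicited at every contact.
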